## Abstract

**Background:**

Patient education, advice on returning to normal activities and (home-based) exercise therapy are established treatment options for patients with non-specific low back pain (LBP). However, the effectiveness of physiotherapy interventions on physical functioning and prevention of recurrent events largely depends on patient self-management, adherence to prescribed (home-based) exercises and recommended physical activity behaviour. Therefore we have developed e-Exercise LBP, a blended intervention in which a smartphone application is integrated within face-to-face care. E-Exercise LBP aims to improve patient self-management skills and adherence to exercise and physical activity recommendations and consequently improve the effectiveness of physiotherapy on patients’ physical functioning. The aim of this study is to investigate the short- (3 months) and long-term (12 and 24 months) effectiveness on physical functioning and cost-effectiveness of e-Exercise LBP in comparison to usual primary care physiotherapy in patients with LBP.

**Methods:**

This paper presents the protocol of a prospective, multicentre cluster randomized controlled trial. In total 208 patients with LBP pain were treated with either e-Exercise LBP or usual care physiotherapy. E-Exercise LBP is stratified based on the risk for developing persistent LBP. Physiotherapists are able to monitor and evaluate treatment progress between face-to-face sessions using patient input from the smartphone application in order to optimize physiotherapy care. The smartphone application contains video-supported self-management information, video-supported exercises and a goal-oriented physical activity module. The primary outcome is physical functioning at 12-months follow-up. Secondary outcomes include pain intensity, physical activity, adherence to prescribed (home-based) exercises and recommended physical activity behaviour, self-efficacy, patient activation and health-related quality of life. All measurements will be performed at baseline, 3, 12 and 24 months after inclusion. An economic evaluation will be performed from the societal and the healthcare perspective and will assess cost-effectiveness of e-Exercise LBP compared to usual physiotherapy at 12 and 24 months.

**Discussion:**

A multi-phase development and implementation process using the Center for eHealth Research Roadmap for the participatory development of eHealth was used for development and evaluation. The findings will provide evidence on the effectiveness of blended care for patients with LBP and help to enhance future implementation of blended physiotherapy.

**Trial registration:**

ISRCTN, ISRCTN94074203. Registered 20 July 2018 – Retrospectively registered.

## Background

Low back pain (LBP) is the most common cause of disability in western society [1]. LBP causes a significant economic burden and is responsible for high direct healthcare costs as well as high indirect costs due to time lost from work [2]. LBP can be caused by a specific pathology or trauma; however, in more than 90% of cases an underlying disease is absent [3, 4]. The clinical course of this so-called ‘non-specific LBP’ varies; some people recover within a couple of days or weeks, and other people experience persistent disabling symptoms leading to chronic LBP [2, 5, 6]. Both national and international clinical LBP guidelines endorse patient education, advice on returning to normal activities and the prescription of home-exercises and/or supervised exercise therapy [7–10].

However, the effectiveness of physiotherapy in patients with LBP does not solely depend on providing the most adequate physiotherapy interventions. It also highly depends on patients’ adherence to prescribed (home-)exercises and recommended physical activity behaviour [11, 12]. Earlier research showed that 45–70% of patients do not adhere to prescribed exercises and physical activity recommendations [13–15], whereas adherent patients with LBP who continue a physically active lifestyle have a reduced risk of recurrent LBP [16]. Therefore, supporting self-management and adherence in patients with LBP is expected to be essential for the effectiveness of physiotherapy interventions on patients’ physical functioning and prevention of recurrent events.

Online applications, such as websites and apps, provide new solutions to support patients’ ability to manage their physical functioning in their home environment, and are promising to support self-management and adherence to prescribed (home-)exercises between face-to-face sessions [17–20]. Consequently, the integration of online applications into healthcare, so-called blended care [21], is expected to have several advantages for patients with LBP. Firstly, a blended intervention can stimulate self-management and exercise adherence to prescribed (home-)exercises and recommended physical activity behaviour in patients with LBP by its 24/7 online support and persuasive design [20, 22–24]. Secondly, the use of online applications enables monitoring and coaching of the patients’ individual health behaviour and provides the physiotherapist with information to optimize and tailor face-to-face care to the patients’ individual needs [22, 23, 25–27].

Despite all these benefits, matching the appropriate blended treatment for the individual patient is reported as a challenge [28]. To resolve this challenge within traditional face-to-face guidance, stratification tools have gained more attention in the last decade. Within a stratified-care approach, the treatment is matched upon the patients’ risk of developing persistent LBP, for example determined with the Keele STarT Back Screening Tool [29]. Research showed that such an approach results in improved physical functioning and satisfaction with care among patients with LBP while reducing costs of healthcare in both physiotherapy [30] – and primary care settings [31, 32]. Whereas the STarT Back Screening Tool can be used for matching the appropriate content of the face-to-face care to the individual patient, this tool also might have the same potential for matching the right digital content to the individual patient. Up until now, no other groups have used a stratification tool for personalization of blended physiotherapy as a whole.

Recently, the authors’ research group developed e-Exercise LBP, a blended and stratified intervention, in co-creation with patients, physiotherapists and experts [33]. E-Exercise LBP consists of face-to-face physiotherapy treatment, in which eCoaching is integrated using a smartphone application. E-Exercise LBP aims to improve patients’ physical functioning by offering a blended stratified-care approach, and consequently influencing patients’ self-management skills and adherence to exercise and physical activity recommendations in a positive way. At the long-term, e-Exercise LBP could result in an improved handling of recurrent LBP and direct and indirect costs. This blended care intervention is an adapted version of previously developed and evaluated blended physiotherapy programs [34, 35]. A pilot study using a prototype of the e-Exercise LBP intervention in 41 patients with LBP demonstrated feasibility and proof-of-concept on functional disability and pain [33]. Based on the results of the pilot study and end-user (patients and physiotherapist) usability experiences, the e-Exercise LBP program was further improved in preparation for the current study.

This study aims to investigate the short- (3 months) and long-term (12 and 24 months) effectiveness on physical functioning and cost-effectiveness of e-Exercise LBP, a primary care based personalized stratified blended care intervention, in comparison to usual primary care physiotherapy in patients with non-specific LBP.

## Method/design

### Study design

A prospective, multicentre cluster randomized controlled trial (RCT) will be conducted. The study has been approved by the Medical Research Ethics Committee of the University Medical Center Utrecht, the Netherlands (ISRCTN 94074203) for all centre sites. Within primary care, e-Exercise LBP will be compared to usual physiotherapy care. A flow diagram of the study protocol is shown in  Fig. 1.

**Fig. 1 Fig1:**
[figure not shown]
RCT study procedures

### Participants

#### Primary care physiotherapy practices

Primary care physiotherapy practices will be invited by letter to participate in the study. Contact details of potential participating practices will be obtained from the professional network of the authors and a previous e-Exercise study [35]. Additionally, a recruitment advertisement will be placed in the online newsletter of The Royal Dutch Association for Physiotherapy (KNGF). Primary care physiotherapy practices are eligible to participate if at least five patients with non-specific LBP consult the practice for physiotherapy treatment each month. Each participating physiotherapy practice will be asked to enrol at least two physiotherapists in order to ensure continuity of care. All primary care physiotherapists, regardless of professional experience and education or specialization (e.g. manual therapist) are eligible to participate.

#### Patients

All patients with LBP who visit a participating physiotherapy practice will be invited to participate in the study.

Eligibility criteria of patients include: (i) being a patient requesting physiotherapy treatment for LBP, defined as pain in the lumbosacral region (sometimes associated with radiating pain to the buttock or leg) [10, 36], (ii) age 18 years or older, (iii) possessing a smartphone or tablet with access to the internet, (iv) mastery of the Dutch language.

Exclusion criteria include: (i) a specific cause of LBP determined through medical imaging or a medical doctor (e.g. osteoporotic fractures, spinal nerve compromise, malignancy, ankylosing spondylitis, canal stenosis, or severe spondylolisthesis), (ii) serious comorbidities (e.g., malignancy, stroke), (iii) current pregnancy, because of the prevalence of pelvic girdle pain as a specific form of LBP.

### Study procedure

Physiotherapy practices that are willing to participate in the study will be screened on eligibility by a researcher (TK or RA). Cluster randomization will be performed at the level of the participating physiotherapy practices. Each practice will be randomly assigned to the intervention (e-Exercise LBP) or the usual care group by an independent researcher using an a priori created computer-generated random sequence table. Physiotherapists in the intervention group will receive two 4-h training sessions about e-Exercise LBP and the study procedures. In the usual care group, physiotherapists will receive one 4-h training session in current best evidence practice according to the guideline LBP of the Royal Dutch Association for Physiotherapy (KNGF) [10] and the study procedures.

Physiotherapists, or their colleagues who will handle the initial registration of the patient, will orally inform potentially eligible patients about the study. Interested patients will receive the patient information letter by e-mail and will be contacted by one of the researchers (TK or RA) by phone prior to the first physiotherapy appointment. When a patient is willing to participate, a face-to-face appointment with one of the researchers (TK or RA) will be scheduled to screen in- and exclusion criteria and to provide written informed consent. After signing informed consent, the patient’s physiotherapist will be informed about the patient’s participation.

During the study period, both patient groups can still receive care from any other healthcare professional.

### Interventions

#### E-exercise LBP

A multi-phase development process based on the Center for eHealth Research (CeHRes) Roadmap [37] was used for development of the e-Exercise LBP intervention [33]. The e-Exercise LBP intervention integrates eCoaching using a smartphone application within face-to-face physiotherapy. The content is based on recommendations from national and international guidelines [7, 8, 10], and preferences and needs of patients and physiotherapists [33]. The principles of stratified care are used to personalize e-Exercise LBP to individual needs [30, 31].

##### Smartphone application

The smartphone application consists of three modules (Table 1): (i) An *information module* containing 12 weekly self-management themes (text and video), including assignments, about the aetiology of LBP, physical activity, patient experiences, pain management, and psychosocial factors related to LBP. (ii) An *exercise module* including a home-based video-instructed exercise program per prognostic risk profile. The selection, frequency and repetitions can be adjusted by the physiotherapist to address the patient’s specific functional limitations. (iii) A *physical activity module* containing a goal-oriented training program consisting of three sessions a week, to maintain or improve the level of physical activity for a self-chosen type of activity (e.g. cycling or walking). The training program starts with a 3-day baseline test, and can be optionally supported by graded activity functionality with tailored feedback, which was previously studied in two osteoarthritis studies [35, 38].

**Table 1 Tab1:**
[figure not shown]
Overview e-Exercise LBP intervention

*LBP* Low back pain, *KNGF* Royal Dutch Association for Physiotherapy, *Max* Maximum

In patients having a “low risk” for developing persistent LBP the smartphone application will offer support for 3 weeks. In “medium” – and “high risk” patients the support will be 12 weeks. Afterwards the content of the smartphone application will remain available for the patients. In “low risk” patients the smartphone application will only contain the information – and exercise modules. In “medium – and high risk” patients the physical activity module will be added. The results of the baseline test of the physical activity module will be used by the physiotherapist and patient to set a goal to reach within 11 weeks. The graded activity functionality can be switched on in “medium risk” patients who avoid physical activity because of LBP. For “high risk” patients the graded activity functionality will always be activated. Print screens of the smartphone application are given in Additional file 1.

##### Face-to-face care

During the first face-to-face session, the physiotherapist will tailor the e-Exercise LBP intervention to the patients’ identified risk for developing persistent LBP (i.e. low, medium or high), using the Keele STarT Back Screening Tool [29, 39, 40] (Fig. 1, Table 1). Patients are asked to schedule their exercises and physical activities in the smartphone application, after which the smartphone application will sent automatic pop-up reminders accordingly. Physiotherapists will be able to monitor patients’ use of the smartphone application, monitor evaluated assignments, and select other types of exercises. With this information, the physiotherapist will be able to evaluate the progress and beliefs of the patients between face-to-face sessions, optimize the content of the smartphone application to patients’ individual needs, and tailor face-to-face care.

Physiotherapists are recommended to provide two face-to-face physiotherapy sessions to patients labelled as “*low risk*”, 8 sessions for patients labelled as “*medium risk*”, and 12 sessions for patients labelled as “*high risk*”. The objective of face-to-face care is to reassure the patient, provide information about LBP, instruct on self-management options, and underline the importance of adequate physical activity behaviour in accordance with the guideline LBP of the Royal Dutch Association for Physiotherapy (KNGF) [10]. Additionally, in medium- and high risk patients, the physiotherapist can consider to provide evidence-based interventions (e.g. passive or active joint mobilization) as recommended by the guideline LBP of the Royal Dutch Association for Physiotherapy (KNGF) [10]. In high risk patients, the physiotherapist will address patient specific psychosocial risk factors using a cognitive behavioural therapy approach, and pain education will be given [41, 42]. However, with respect to the physiotherapists’ clinical competences, physiotherapists are allowed to deviate from the e-Exercise protocol.

After completing e-Exercise LBP, the patient will receive fortnightly reminders from the smartphone application for up to 6 months to continue a physically active lifestyle.

#### Usual care

Patients in the usual care group will receive face-to-face usual care following the recommendations of the guideline LBP of the Royal Dutch Association for Physiotherapy (KNGF) [10]. Although eCoaching applications are not recommended in the guideline, physiotherapists from the usual care group are instructed to treat people without using any eCoaching applications. According to the guideline, the physiotherapy treatment includes information, exercises, and recommendations regarding physical activity. Practical content considerations will be made by the physiotherapists themselves with respect to their clinical expertise. The number of sessions will differ per patient.

### Measurements

Four time points (baseline, 3, 12 and 24 months) will be used for data collection of the primary and secondary outcomes using an online questionnaire. Baseline measurement will be conducted face-to-face and follow-up measurements preferably through online communication, e.g. Skype or FaceTime. When follow-up measurements through online communication are not possible, follow-up measurements will be conducted face-to-face. At all four time points participants will receive an accelerometer (Activ8) for the objective measurement of physical activity. Participants will be instructed to wear the Activ8 for five consecutive weeks at baseline and eight consecutive days at all following time points, except during sleeping, showering, bathing or swimming. For the economic evaluation, patients will be asked to complete eight retrospective 3-monthly online cost questionnaires. All of these questionnaires will have a 3-month recall period to cover the full duration of follow-up (i.e. 24 months). No financial incentives to complete questionnaires or to wear accelerometers will be offered. Table 2 gives a summary of all outcome measures and time points.

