#### Effectiveness

The primary purpose of this study is to estimate the effectiveness of e-Exercise LBP for improving physical functioning compared to usual primary care physiotherapy in patients with LBP. The primary analysis time point for the study will be 12 months following baseline, however 3- and 24-month changes will also be evaluated. To evaluate the overall effectiveness of e-Exercise LBP, differences in change scores per group and time period will be estimated on primary and secondary outcomes using linear mixed models (LMM) with random effects to control for correlation within patients and physiotherapists [70, 71]. The three-level hierarchy will exist of repeated measurements (level 1), nested within patients (level 2), nested within physiotherapists (level 3). Analysis will be controlled for baseline variables that have been shown to be related to physical functioning, e.g. age, gender, pain severity scores, duration of pain [72–74].

In addition, a per-protocol analysis that only includes patients of the intervention group which were adherent to the smartphone application and the entire usual care group will be performed. Patients will be considered to be adherent to the smartphone application if they used the application for at least 2/3rd of the duration (i.e. 2 out of 3 week for the “low-risk” profile and 8 out of 12 weeks for the “medium- and high-risk” profile) [35, 75]. Per-protocol analyses will be performed using LMM with the same 3-level structure, and will be controlled for the same variables as the primary analysis.

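### The five-week baseline accelerometer window very likely includes treated days, so change scores for physical activity can subtract part of the treatment effect

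*Protocol article*

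**What the plan says.** The Measurements section of the protocol article fixes the wear periods: patients are to "wear the Activ8 for five consecutive weeks at baseline and eight consecutive days at all following time points". The abstract times the assessments from enrolment: "All measurements will be performed at baseline, 3, 12 and 24 months after inclusion".

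Study procedure gives the order of events. Interested patients are contacted "by phone prior to the first physiotherapy appointment". They then attend a screening and consent visit, after which the "physiotherapist will be informed about the patient" taking part. No run-in and no pause before treatment is described.

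The text below Table 1 gives the length of app support. For low-risk patients "the smartphone application will offer support for 3 weeks"; for medium- and high-risk "patients the support will be 12 weeks". Only the medium- and high-risk groups receive the physical activity module.

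Accelerometer-measured physical activity is listed under Secondary outcome measures. The Effectiveness section states that "differences in change scores per group and time period will be estimated on primary and secondary outcomes using linear mixed models".

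**The concern.** A baseline value is meant to describe the patient before the arms can differ. Here the patient is already seeking physiotherapy, and the device is worn for 35 days from about the time of enrolment. If treatment starts within those 35 days, part of the value called baseline is recorded under the allocated treatment.

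A change score then subtracts whatever between-arm difference has already appeared. The same happens in a mixed model that takes baseline as one of the repeated measurements, because the group-by-time contrast is a difference in change. Neither the random effects nor the multiple imputation removes this.

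The stake is one secondary outcome, but a relevant one. The app is meant to raise adherence to physical activity recommendations, and for medium- and high-risk patients it contains a training programme aimed at this behaviour. A real effect on activity could be reported as smaller than it is.

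**Working it through.** The plan gives no figure for the physical activity effect, so there is none to reproduce. Its sample size rests on the ODI alone.

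**Inputs from the protocol article**
- Baseline wear: 5 weeks = 35 days (Measurements).
- Follow-up wear: 8 days at 3, 12 and 24 months (Measurements).
- App support: 3 weeks for low risk, 12 weeks for medium and high risk (text below Table 1).
- Time origin: inclusion (abstract, Methods).

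**Inputs not in the document, assumed**
- Lag *L* from the start of wear to the first session: 0, 1 or 2 weeks.
- Onset: the between-arm effect is zero until *L*, rises linearly to its full size over *R* = 3, 6 or 12 weeks, and then stays constant.

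**Step 1. Could treatment wait until the window ends?** Then 12 weeks of support would finish at week 5 + 12 = 17. The 3-month measurement falls at about week 13. A start soon after baseline fits this schedule much better than a five-week hold.

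**Step 2. Overlap with treatment.** The share of the window after treatment start is (35 − lag in days)/35:
- lag 0: 35/35 = 100%
- lag 1 week: 28/35 = 80%
- lag 2 weeks: 21/35 = 60%

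The part of a 12-week programme inside the window is (5 − *L*)/12, which is 42%, 33% and 25% for the three lags. The 3-week low-risk programme lies wholly inside the window for any lag up to 2 weeks.

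**Step 3. Fraction of the full effect contained in the baseline mean.** If all 35 days are averaged, this is the mean over the window of the onset curve:
- if *L* + *R* ≤ 5: (5 − *L* − *R*/2)/5
- if *L* + *R* > 5: (5 − *L*)²/(10*R*)

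| Lag | *R* = 3 weeks | *R* = 6 weeks | *R* = 12 weeks |
|---|---|---|---|
| 0 | 3.5/5 = 70% | 25/60 = 42% | 25/120 = 21% |
| 1 week | 2.5/5 = 50% | 16/60 = 27% | 16/120 = 13% |
| 2 weeks | 1.5/5 = 30% | 9/60 = 15% | 9/120 = 7.5% |

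The fraction is zero only if treatment starts 5 or more weeks after baseline.

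**Step 4. How much is due to the window length?** With an 8-day window like those at follow-up (8/7 = 1.14 weeks), the fraction at lag 0 is 1.14/(2*R*): 19% for *R* = 3 and 5% for *R* = 12. At a lag of 1 week it is below 1%. Most of the problem comes from the five weeks.

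**The case against.** **The overlap is inferred.** The interval from the baseline visit to the first session is nowhere stated, and Fig. 1 and Table 2, which may show it, are not available in the text reviewed. This stands as a limit on certainty. It does not reverse the conclusion, because avoiding overlap needs a hold of at least five weeks that no passage describes and that fits badly with the 3-month timing.

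**A wear instruction is not a definition of the baseline value.** The device stores summaries every 5 minutes, so a shorter pre-treatment window could be extracted, and such rules are often left to an analysis plan. That is fair. But the article itself fixes five weeks as the wear period at baseline and fixes change scores as the analysis. Followed as written, the two together give a contaminated baseline.

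**Some stronger readings are not supported.** A reader might infer that 40% to 50% of the effect is lost. That follows only from assuming that half the 3-month effect is present on average over the treated days. Goal-setting over 11 weeks in the activity module suggests a slower onset, and hence a smaller loss. A reader might also take it that at least a third of the 12-week programme lies in the window, but this holds only for a lag of 7 days or less. The complete overlap in low-risk patients looks striking, yet that group does not receive the activity module. Usual care also includes activity advice, so only the between-arm difference within the window is subtracted, not the whole early change. Finally, bias through covariate adjustment cannot be claimed, because the covariates given as examples do not include baseline activity.

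***Weeks* may be a slip for *days*.** If so, most of the problem goes away and one word needs correcting.

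**Conclusion.** The point holds as a likely contamination of the baseline, not a proven one. As written, the baseline accelerometer window very probably includes treated days, and the change-score analysis would subtract any between-arm difference in activity already present. The bias is towards no difference, provided that the effect has the same direction throughout.

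Its size is not fixed by the documents. It runs from about 7.5% to 70% of the full effect for lags of 0 to 2 weeks and linear onset over 3 to 12 weeks, if all 35 days are averaged and the effect is sustained to follow-up. No single figure within that range is better supported than another.

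One secondary outcome is affected. The ODI primary outcome and the sample size are untouched. The wording should be corrected because the fix is cheap and the outcome is one that the app targets directly.

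**What to change.** 1. State whether the baseline wear period is five weeks or five days. If *weeks* is a slip, correct it.
2. If five weeks is intended, define baseline activity from valid wear days before the first physiotherapy session only. Fix in advance the minimum number of valid days and apply it alike in both arms.
3. Report the remaining days of the five weeks as a separate early on-treatment measure.
4. Where pre-treatment days are too few, compare follow-up activity between arms instead of change from a contaminated baseline.

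**Cost.** The change needs wording, the date of each first session, and date filtering of stored data; no new measurement is needed. The loss of baseline information can be substantial. Lags of 0, 3 or 7 days leave about 0, 3 or 7 pre-treatment days, so patients treated at once have no usable baseline. For them the analysis loses the precision that a baseline gives and relies on the randomisation of practices for balance in prior activity. That is a real price, but it is confined to this secondary outcome.
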